## Abstract

**Background:**

The consumption of tobacco is regarded as a contributing factor to several diseases. However, the impact of tobacco dust exposure (TDE) on tobacco workers has not been extensively investigated.

**Objective:**

This protocol introduces the design and implementation of the Tobacco Dust Cohort for Health Assessment and Risk Monitoring (T-CHARM) study, a prospective cohort study aimed at evaluating the health impacts of TDE.

**Methods:**

This prospective cohort study will recruit women working in tobacco processing who are nonsmokers and women who do not work for the tobacco industry and are nonsmokers living in a nearby area (unexposed group), with a total of 400 expected participants. The impact of TDE on health, including metabolic syndrome parameters; complete blood count; and cardiovascular, liver, renal, and lung function, will be evaluated in relation to urine cotinine levels. Air quality and chemical substances in the air and leaves will also be analyzed. The data will be subsequently analyzed using appropriate statistical tools.

**Results:**

A total of 120 respondents have participated as of August 2025. Another 80 respondents will be recruited, laboratory analysis is ongoing, and baseline results are expected by the end of 2025.

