#### Bioindicator Sampling

Tobacco leaves are also collected to study the accumulation of airborne pollutants, particularly radionuclides and heavy metals, as bioindicators of environmental exposure.

Figure 3 illustrates the recruitment process for the T-CHARM study. The exposed group consisted of a total population of 2333 women who work in tobacco processing, of whom 1816 met the eligibility criteria following screening. From this eligible pool, a target sample of 200 participants was estimated and recruited. To ensure comparability, the unexposed group—women who were nonsmokers and residents of nearby communities—was also designed to include 200 participants, matched by key demographic and environmental factors. The total cohort size for follow-up is projected to reach 400 participants, with data collection encompassing baseline and longitudinal health metrics. All collected data are subjected to analysis using appropriate statistical tools, as outlined in the study’s analysis plan.

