## Results

The T-CHARM study was officially funded in the year 2024, with data collection commencing in July 2024. As of August 2025, the study has successfully enrolled 60 participants in each group—women who are nonsmokers and work in tobacco processing (exposed group) and women who are nonsmokers and community members (unexposed group). Recruitment for an additional 80 participants is currently underway, alongside laboratory analyses for the second phase of baseline data collection. These analyses include biomarker profiling, clinical assessments, socioeconomic status, and environmental exposure measurements. The cohort baseline results are expected to be published by the end of 2025, marking a key milestone in the study’s longitudinal design and setting the foundation for future follow-up waves.

In general, among the 60 women recruited for the exposed group, most of them were obese (n=28, 46.7%) and overweight (n=11, 18.3%), 76.7% (n=46) were of Madurese ethnicity, 53.3% (n=32) had education in elementary school, and 45.0% (n=27) were educated until middle and high school. Their mean age was 40 (range 21-52) years. Compared to the other work in that area, tobacco workers are paid well, with 76.7% (n=46) having an income as high as 875,000 IDR (US $52.50). Another key finding is that all the study participants are nonsmokers but exposed to tobacco dust occupationally, and 57.1% (n=60) reported being passive smokers. Health questionnaire answers showed that 60 people complained of eye problems, 28 had dermatological issues, 5 had respiratory diseases, 11 had cardiovascular disease, 60 had neurological problems, and 37 had reproductive issues.

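### The recruitment figures (120 enrolled, 80 to come) are not reconciled with the stated cohort of 400, and 200 exposed women are called recruited when 60 are enrolled

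*Protocol article*

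**What the plan says.** **Planned size.** The Abstract (Methods) describes a study of exposed and unexposed women "with a total of 400 expected participants". The recruitment paragraph in the Methods, printed under Bioindicator Sampling, gives the breakdown. For exposed women: "From this eligible pool, a target sample of 200 participants was estimated and recruited". The unexposed group "was also designed to include 200 participants, matched by key demographic and environmental factors". The paragraph then says: "The total cohort size for follow-up is projected to reach 400 participants".

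**Recruitment status.** The Abstract (Results) states: "A total of 120 respondents have participated as of August 2025". It goes on: "Another 80 respondents will be recruited, laboratory analysis is ongoing, and baseline results are expected by the end of 2025". The Results section agrees and gives the split: "As of August 2025, the study has successfully enrolled 60 participants in each group". It also reports that recruitment of 80 further participants is in progress, mentions laboratory work for a second stage of baseline collection, and expects the cohort baseline results to be published by the end of 2025.

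**The concern.** The article gives its size in two ways, and they do not meet. The planned figure is 400. The enrolled and still-to-recruit figures, added together, give 200. A reader cannot tell whether the cohort is still 400 with most recruitment ahead, or has in practice become 200.

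A second mismatch lies in the exposed group alone. The Methods paragraph reports the sample of 200 as already recruited, while the Results section has 60 exposed women enrolled.

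The size matters here because the article gives no power calculation, so the head count is the reader's only guide to precision. It also sets the starting number for a follow-up of up to 20 years in which the article itself names loss to follow-up as a limitation.

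**Working it through.** **Inputs, all from the protocol article**
- Exposed target 200, unexposed target 200, total 400 (Methods, recruitment paragraph; the total also in Abstract, Methods)
- Enrolled 120 in total (Abstract, Results), 60 per group (Results)
- Still to recruit: 80 (Abstract, Results; and Results)

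**Step 1. The plan's own figure.** 200 + 200 = 400. The design total is consistent with its parts.

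**Step 2. The enrolled figure.** 60 + 60 = 120. The Abstract and the Results section agree.

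**Step 3. Do the recruitment figures lead to 400?**

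| Reading of the 80 | Sum | Total | Share of 400 |
|---|---|---|---|
| 80 in total | 60 + 60 + 80 | 200 | 50% |
| 80 per group | 2 × (60 + 80) | 280 | 70% |
| 120 and 80 both per group | 2 × (120 + 80) | 400 | 100% |

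The third reading reaches 400, but the Results section rules it out by stating that "the study has successfully enrolled 60 participants in each group". The first reading leaves 400 − 200 = 200 women unaccounted for; the second leaves 400 − 280 = 120.

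**Step 4. What 400 would need.** 400 − 120 = 280 more women, or 140 per group.

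**Step 5. The exposed group.** 200 described as recruited, less 60 enrolled, leaves a gap of 140.

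**Step 6. Illustration of what the size means for precision.** The article gives no effect size, SD or power, so no power-based sample size can be reproduced. I assume a two-sided 5% level (the Group Comparisons section gives the 5% but not the sidedness), 80% power and equal groups of n. The detectable difference in SD units is (1.960 + 0.842) × √(2/n):
- n = 200: 2.802 × √0.0100 = 0.280
- n = 140: 2.802 × √0.0143 = 0.335
- n = 100: 2.802 × √0.0200 = 0.396

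The exact two-sample t calculation gives 0.281 at 200 and 0.398 at 100 per group, so 0.28 and 0.40 to two decimals. The width of a confidence interval for a mean difference changes by √(200/100) = 1.41 between 200 and 100 per group, that is, 41% wider.

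**The case against.** The strongest reply is that a target and a dated status report can both be true. Every statement of 400 looks forward: it is expected, or projected. The 120 and the 80 describe the position in August 2025. The mention of a second stage of baseline collection, and the Conclusions' reference to the current phase of the study, make staged recruitment a live possibility. The recruitment flowchart (Figure 3) is not visible in the text at hand and may carry counts or stages.

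Much of this stands, and it limits the point in four ways.
- A reader might infer that the cohort has been cut to 200. The article does not say so: nowhere does it state that the 80 completes recruitment.
- A reader might infer that the end-2025 baseline report will rest on exactly 200 women. The article lists the recruitment, the laboratory work and the report side by side without tying the report to a number.
- A reader might take both groups of 200 as reported recruited. The verb applies only to the exposed group, and it is paired there with a target, which suggests loose wording.
- A reader might say that planned power is lost. No power or precision is stated, so none is breached. The 0.28 SD is simply what 200 per group detects at an assumed 80% power.

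The reply does not remove the problem. The visible text never says that the 80 is one instalment, never mentions a later one, and presents the end-2025 results as those of the cohort, not as interim. Staging also cannot explain why 200 exposed women are called recruited when 60 are enrolled. Nor is this a matter of a condensed article leaving detail out: the target and the recruitment figures are each printed twice, and they do not fit together.

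**Conclusion.** The point holds as a failure to reconcile the recruitment figures with the stated cohort size. On the visible text, enrolled plus remaining gives 200, or 280 if the 80 is per group, against a stated 400. The statement that 200 exposed women were recruited cannot stand beside 60 enrolled.

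The head count needs no assumption beyond the article's own numbers. Which figure the sponsor intends cannot be settled from the document. The precision figures (0.28 SD against 0.40 SD, intervals about 41% wider) are illustrative: they rest on an assumed two-sided 5% level and 80% power, and they apply only if the final cohort is 200. Because total sample size is a basic design fact and the two readings can differ twofold, the text should be corrected before the cohort is cited or its baseline reported.

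**What to change.** Use one set of figures in the Abstract (Methods and Results), the recruitment paragraph of the Methods, and the Results section: the target per group and in total, the number enrolled with its date, the number remaining, and any phasing.
- If 400 stands, say that 280 remain (140 per group), state when the groups beyond the current 80 would join, and label the end-2025 report as an interim baseline with its actual number.
- If the 80 is the full remainder, restate the cohort as 200 (100 per group). If the 80 was meant per group and is the full remainder, the figure is 280 (140 per group).
- In the recruitment paragraph, describe the 200 exposed women as targeted, not recruited.
- Check that Figure 3 carries the same counts.

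The cost is a text correction. No extra participants and no change of analysis are needed to put the figures right; if 400 stands, the further 280 women are already implied by the plan.

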**Conclusions:**

The strength of the T-CHARM study’s approach is its detailed occupational and environmental factors and longitudinal health data from the corporate clinic or the district health center, as well as links to cancer and mortality registries and self-reported health. The current phase of the study focuses on baseline data collection for long-term follow-up. The cohort will be monitored for up to 20 years, depending on sustained funding. T-CHARM offers a robust framework for understanding the chronic health effects of occupational TDE.

**International Registered Report Identifier (IRRID):**

DERR1-10.2196/84231

## Introduction

The tobacco industry is one of the biggest industries and provides millions of jobs [1]. In Indonesia, Jember Regency has long been recognized as “Tobacco City,” reflecting its deep-rooted economic and cultural ties to tobacco cultivation and processing [2]. While most research on tobaccosis (chronic tobacco poisoning) has focused on people who smoke, there is a gap in studies examining occupational exposure, particularly among workers in tobacco processing environments who do not smoke [3]. The health effects of tobacco dust exposure (TDE), especially from nicotine-laden particulates, remain poorly understood despite growing concern [4]. This lack of data is critical, as workers may experience chronic exposure without direct tobacco use. Addressing these issues is complex, as the tobacco industry intersects with economic welfare, government policy, and political influence, making regulatory and public health interventions particularly challenging [5,6].

A study was conducted to investigate the concentration of tobacco dust in a tobacco factory in Thessaloniki, Greece. The findings revealed a markedly elevated level of total suspended dust in the workplace, with concentrations ranging from 45.3 to 54.4 μg/m^–3^ [7]. Nicotine has been demonstrated to elevate both blood pressure and heart rate, and to induce atherogenesis in coronary artery endothelial cells [8]. This is attributed to its sympathomimetic effects, which result in an increased heart rate, myocardial contractility, elevated coronary vascular resistance, and decreased insulin sensitivity. Consequently, there is an increased risk of developing cardiovascular diseases, including coronary heart disease and atherosclerosis [9].

This research builds on a 2015 study that yielded notable insights into the impact of TDE on worker well-being [4]. The issue of workers’ health is frequently overlooked due to a lack of knowledge and the absence of the requisite infrastructure, with the health of workers in the tobacco industry being of particular concern. Further evaluation is required to ascertain the effects of chronic TDE, which will be conducted using a prospective cohort study design. We will use an observational design with a cross-sectional method as a preliminary baseline for a prospective cohort study. A future cohort study is anticipated to ascertain the definitive effects of TDE, circumventing the inherent biases of cross-sectional research [10]. The nature of TDE exposure shares similarities with thirdhand smoke, the residual tobacco pollutants that linger on surfaces and in dust, posing risks even in the absence of active smoking. Therefore, the findings from this study are expected to benefit not only tobacco workers but also individuals exposed to thirdhand smoke in residential and occupational settings.

## Methods

### Study Design

The Tobacco Dust Cohort for Health Assessment and Risk Monitoring (T-CHARM) study examines how occupation and the environment of an agricultural area (especially tobacco) can cause diseases and affect people’s well-being over time.

Starting in 2024, the T-CHARM cohort is based on a tobacco factory and its surrounding areas under the jurisdiction of the Ajung Health Center in Jember, Indonesia (Figure 1). The study is led by local research teams from a regional university in collaboration with international partners from Kagoshima University (Japan), the University of Occupational and Environmental Health (Japan), and the National Research and Innovation Agency (Indonesia).

The project is supported by a range of funding sources, including Directorate of Research and Community Service (Direktorat Penelitian dan Pengabdian kepada Masyarakat), Indonesia; Japan’s Ministry of Education, Culture, Sports, Science and Technology; and institutional grants and travel programs from participating universities in both Indonesia and Japan.

**Figure 1 figure1:**
[figure not shown]
Geographic location of study groups in the Tobacco Dust Cohort for Health Assessment and Risk Monitoring (T-CHARM) cohort. This map illustrates the research location of the T-CHARM study in Ajung District, Jember Regency, East Java, Indonesia. The gray-shaded area represents Ajung District, where both the exposed group (nonsmoking women tobacco processing workers) and the unexposed group (nonsmoking women workers from nontobacco occupations) were recruited.

### Study Population and Eligibility Criteria

The T-CHARM study recruited participants from one of the largest tobacco processing industries in Jember, Indonesia, which employs approximately 2333 women in its processing section and is certified by international occupational and safety standards.

#### Exposed Group

Participants in the exposed group are women who work in tobacco processing who are nonsmokers. These individuals are regularly exposed to tobacco dust and related particulates through their occupational activities.

#### Unexposed Group

The comparison group consisted of women who are nonsmokers and employed in occupations unrelated to tobacco within the same district as the tobacco factory. This geographic proximity helps to control for environmental factors unrelated to occupational exposure.

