### Data Collection Method

#### Overview

Baseline data for the T-CHARM study were collected through direct, face-to-face interviews conducted by researchers, with support from physicians and trained surveyors. Data collection took place at the tobacco factory and associated workplaces. A structured questionnaire was administered, comprising closed-ended questions across multiple domains, including sociodemographic information, duration of employment, medical history, smoking status, menstrual history [11], hydration status, ergonomic concerns [12], physical activity levels [13], sleep quality [14], anxiety potential [15], and tobacco exposure assessment.

In addition to the questionnaire, a series of clinical and physiological examinations were performed to evaluate the general health status of participants. These included vital signs assessment [16], BMI calculation, ergonomic observation [17], pulmonary function testing using a portable spirometer (Contec SP10, Contec Medical System Co, Qinhuangdao, Hebei, China) [18], and venous blood sampling (3 mL) for serum analysis, including complete blood count, blood glucose, lipid profile, liver function, and renal function tests. Furthermore, a random urine sample was collected in a sterile container to analyze urine profile and cotinine levels, adjusted for creatinine concentration, using an enzyme-linked immunosorbent assay. To monitor longitudinal changes in health parameters, the same data collection protocol will be repeated every 5 years over 20 years (Figure 2).

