#### Group Comparisons

Comparative analyses between the exposed and unexposed groups will be performed for respondent characteristics, health examination results, medical history, lung function, and blood and urine parameters. Statistical tests will include Student *t* test for continuous (ratio) variables and Pearson *χ*^2^ test or Fisher exact test for categorical variables, and *P* values <.05 will be considered statistically significant.

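### The unexposed group is defined by present work or residence, with no rule on past tobacco work, and is described inconsistently as employed workers or as community residents

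*Protocol article*

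**What the plan says.** The protocol article describes the comparison group in five places.

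- Unexposed Group: nonsmoking women "employed in occupations unrelated to tobacco within the same district as the tobacco factory".
- Figure 1 caption: "nonsmoking women workers from nontobacco occupations".
- Abstract, Methods: "women who do not work for the tobacco industry and are nonsmokers living in a nearby area (unexposed group").
- Bioindicator Sampling (the paragraph on recruitment): "women who were nonsmokers and residents of nearby communities".
- Results, reporting the 60 already enrolled: "women who are nonsmokers and community members (unexposed group").

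The Inclusion Criteria are written for all participants. They require age 18 to 55, nonsmoking confirmed by self-report and urine cotinine, good health at recruitment, and active work as a labourer for at least 8 hours a day, 6 days a week. The Exclusion Criteria cover fever or diarrhoea and any condition that could confound the assessments. Neither list mentions previous tobacco work.

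The questionnaire (Data Collection Method, Overview) covers duration of employment and, at the end of its list, "sleep quality [14], anxiety potential [15], and tobacco exposure assessment". The article does not link these items to eligibility or to group assignment.

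**The concern.** The study asks about chronic, even lifetime, exposure to tobacco dust, but it separates exposed from unexposed women by what they do now. The Introduction describes the regency as economically and culturally tied to tobacco growing and processing. One company employs about 2333 women in processing, and the comparators come from the same district. Former processing workers among local women of working age are plausible, and nothing in the criteria keeps them out of the reference group. Where past exposure has left an effect, their inclusion dilutes the contrast, and more recruitment does not remove that bias.

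The second problem is which women are being compared. If comparators must be full-time labourers, the contrast is between labourers in and outside tobacco. If they need only live nearby, exposure is mixed with employment itself. The article can be read either way for the women already in the cohort.

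**Working it through.** **Text comparison**

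| Place | Employment required of comparators? | Past tobacco work addressed? |
|---|---|---|
| Unexposed Group | Yes, outside tobacco | No |
| Figure 1 caption | Yes, outside tobacco | No |
| Inclusion Criteria (all participants) | Yes, full-time labourer | No |
| Exclusion Criteria | Not mentioned | No |
| Abstract, Methods | Not stated; lives nearby, not in the tobacco industry | No |
| Bioindicator Sampling | Not stated; resident nearby | No |
| Results | Not stated; community member | No |

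The cotinine check is stated as confirmation of nonsmoking and says nothing about past jobs. The open-ended exclusion refers to a condition and does not name work history.

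**Illustration of size**

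The article gives no effect size, no SD, no power statement and no share of former workers, so there is no figure to reproduce. The inputs are:

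- n = 200 per group, stated under Bioindicator Sampling.
- n = 100 per group as an alternative: 60 + 60 = 120 enrolled, plus 80 still to recruit (Abstract, Results; Results), makes 200, assumed to be split equally.
- Significance level 0.05, from Group Comparisons; two-sided is assumed.
- True difference δ = 0.40 SD (assumed).
- Share c of former workers among comparators = 10%, 20% or 30% (assumed).
- Each former worker carries the full effect seen in current workers (assumed; this is the worst case), and the SD is unchanged.

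Reference mean = (1 − c)μ₀ + cμ₁, so the observed difference is (1 − c)δ.

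Power ≈ Φ((1 − c)δ·√(n/2) − 1.96).

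The sample needed for fixed power is multiplied by 1/(1 − c)².

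| c | Observed difference | Power, 200 per group | Power, 100 per group | Sample multiplier |
|---|---|---|---|---|
| 0 | 0.40 SD | 98% | 81% | 1.00 |
| 10% | 0.36 SD | 95% | 72% | 1.23 |
| 20% | 0.32 SD | 89% | 62% | 1.56 |
| 30% | 0.28 SD | 80% | 51% | 2.04 |

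Worked example, c = 20% and n = 200: 0.80 × 0.40 = 0.32; 0.32 × √100 = 3.2; 3.2 − 1.96 = 1.24; Φ(1.24) = 0.89.

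For a smaller effect, take the difference that 200 per group detects with 80% power. This is √(2/200) × (1.96 + 0.84) = 0.28 SD. With c = 10%, 20% or 30% the observed difference is 0.252, 0.224 or 0.196 SD and power is 71%, 61% or 50%. Restoring 80% power would take 247, 313 or 409 per group.

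**The case against.** The strongest reply is that the eligibility rules already do much of the work. They apply to both groups and require good health and full-time labouring work. A former tobacco worker could enter only if she is now healthy and holds another full-time job. A reader might infer that women who left the factory through illness would fill the reference group and reverse the effect. The health criterion makes that unlikely, although changes short of overt illness could still pass.

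A reader might also infer that labourers are being compared with women who do not work, and so that a healthy-worker bias is present. The documents do not show this. An employed labourer can also be a resident and a community member, and the inclusion criteria, if applied, rule out women without such work. What stands is that three descriptions leave the condition out, one of them the report on women actually enrolled.

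It can further be said that a fuller definition may sit in a full protocol not shown, and that the questionnaire may record past work. That is possible. But the article itself sets out the definition and the criteria, and nothing in it connects work history to group membership. The planned matching on demographic and environmental factors and the optional strata by length of employment do not name past exposure either.

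Finally, the power figures rest on assumed inputs. At the stated 200 per group and 0.40 SD the loss is modest. The fall to 51% needs both 100 per group and the worst assumed share.

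**Conclusion.** The point holds in two limited parts. First, as written, a healthy and currently employed former tobacco-processing worker qualifies as unexposed, which biases group differences toward no effect in a study of chronic exposure. Second, the comparator is an employed worker in some places and simply a resident in others, so the rule applied to the 60 already enrolled cannot be determined.

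The direction of the bias follows from the definition, provided past exposure has some lasting effect. Its size cannot be derived from the document. If former workers carry the full effect, the observed difference shrinks by exactly their share. The document supports neither a reversed effect nor a demonstrated healthy-worker bias. The change should be made now, while comparators may still be recruited; it becomes harder to make later in a cohort planned for up to 20 years.

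**What to change.** 1. Use one definition in the Abstract, Figure 1, Methods and Results: currently employed full time as a labourer outside tobacco, as in the Unexposed Group section and the Inclusion Criteria. State whether the 60 enrolled comparators met it.
2. For comparators still to be recruited, add the criterion that the woman has never been employed in tobacco processing.
3. For the 60 already enrolled, record past tobacco work from the employment and tobacco-exposure questionnaire items, and ask again where these are silent. Exclude former processing workers from the main comparison and report results with and without them.
4. Record past tobacco growing and tobacco workers in the household for sensitivity analysis only. Making either an exclusion could narrow the comparator pool in a tobacco district and make the groups less alike.

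The cost is a few questions, consistent wording and some re-contact. The downside is somewhat slower recruitment of comparators and the loss of some enrolled women from the main comparison.
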